### 3.0 Objectives/Aims

We propose a randomized, controlled trial to evaluate the effectiveness of an mHealth Diabetes Adherence Support (*mDAS*) intervention delivered by clinical pharmacists and health coaches. This proposal is in response to NIH PA-14-334: Advancing Interventions to Improve Medication Adherence. We will randomize 220 patients through the University of Illinois Hospital & Health Sciences System (UI Health) to either: (1) mHealth diabetes adherence support (*mDAS*) through clinical pharmacists and HCs; or (2) usual care. After one year, patients completing the mHealth adherence intervention will be monitored for an additional year while the usual care group receives *mDAS*.

The specific aims include:

- Aim 1:** To evaluate the *effectiveness* of *mDAS* delivered by clinical pharmacists and HCs to African-American and Latino adults with uncontrolled type 2 diabetes. We will compare *mDAS* and usual care through the following outcome measures: hemoglobin A1c, blood pressure, LDL-cholesterol levels, and medication adherence.
- Aim 2:** To evaluate the *maintenance* of improved clinical outcomes and medication adherence one year after intervention completion.
- Aim 3:** To evaluate the cost and cost-effectiveness of *mDAS* compared to usual care.
- Aim 4:** To evaluate *reach, adoption, and implementation* of *mDAS* (RE-AIM framework)

### 3.1 Objectives/Aims for mDAS Sub-study Sleep Supplement

Sleep quality and duration are increasingly being recognized as modifiable risk factors for improving diabetes control. Studies have shown that short sleep duration (less than 7 hours), long sleep duration (more than 8 hours), and poor quality of sleep are associated with impaired glucose tolerance and insulin resistance. This increases the risk of developing diabetes and worsens glycemic control among those with type 2 diabetes. Research specifically targeting sleep among low-income African-Americans and Latinos is lacking; however, available data suggest that these groups are more likely to experience problematic sleep patterns resulting in detrimental metabolic effects of poor sleep. In addition, clinicians rarely assess sleep, though they are available to intervene on sleep hygiene. Collectively, these factors support the need to further investigate sleep in low-income minority populations with diabetes with intentions of developing remotely-delivered sleep assessment and intervention. The overall objectives of this study are to characterize sleep quality and duration among African-Americans and Latino-Americans with uncontrolled diabetes, evaluate the effectiveness of mHealth in monitoring sleep quality and duration, and explore the relationships between sleep and glycemic control.

The specific aims of this proposed study include:

**Aim 1:** To explore subjective daily sleep quality, duration, and patterns of 40 inner-city African-American and Latino-American patients with poorly controlled type 2 diabetes (hemoglobin A1c $\geq$ 8%). Sleep quality, duration, and patterns will be measured by a validated sleep questionnaire, a mHealth version of a validated consensus sleep diary, and a home sleep environment questionnaire.

**Aim 2:** To evaluate the feasibility and acceptability of objectively measuring sleep quality, duration, and patterns and sedentary behaviors via mHealth. Study participants will wear an Actigraph Watch for seven days (including nights) and report their experiences with the device and assess its acceptability.

**Aim 3:** To explore the relationships between subjective and objective measures of sleep quality, duration, and patterns, as well as the relationships between the sleep measures, glycemic control (i.e., hemoglobin A1c), quality of life, depression, and sedentary behaviors.

Hypotheses 3a: Poorer sleep quality, duration, and patterns will be associated with higher hemoglobin A1c levels.

Hypotheses 3b: Poorer sleep quality, duration, and patterns will be associated with a lower quality of life, depression and more sedentary behaviors.

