#### **Additional information for mDAS Sleep Sub-study Supplement**

5. English-speaking participants will be asked to participate in a sleep sub-study to evaluate his or her sleep for 9 days at one of the regularly scheduled data collection follow up visits for the parent study.
6. RAs will screen willing participants for the sleep sub-study for eligibility and discuss the study protocol in detail. If the patient is interested, he/she will complete written informed consent for the sleep sub-study and complete the questionnaires. He/she will take an actiwatch to wear day and night for 7 days. Each day, they will receive mytapp messages asking about their sleep quality and process the night before. The Actiwatch will be returned at patient's convenience (drop it off or RA will pick it up). Reimbursement for the entire study is \$40.

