#### **Additional Data Collection for mDAS Sub-study Supplement**

7. Each subject will be asked to complete surveys in interview format on personal sleep practices. The surveys include: Pittsburgh Sleep Quality Index, PROMIS Sleep-related Impairment Short Form 8a (8 items) and PROMIS Sleep Disturbance Short Form 8b (8 items), an assessment of sleep apnea and restless leg syndrome. This will take approximately 20 minutes. Patients will be compensated \$10 for this initial sleep sub-study data collection.
8. The RA will provide instructional tutorial on using the wrist actigraphy (Actiwatch) to the participants. This will take approximately 5 minutes
9. Study participants will wear a wrist actigraphy for 7 days and 7 nights and answer custom questions on sleep after the participants wake up. The participant has the option of answering the questions via myTapp messages or through a web-based online sleep diary survey using a secure application such as REDCap or Qualtrics. These questions will be modified from a validated consensus sleep diary.
10. At the end of the 9 days, participants will be telephoned to complete a post-study evaluation and to schedule a day/time to return the actigraph watch.
11. Participants will be compensated \$30 for sub-study completion by research personnel.

**On the consent form, participants will be asked for permission to use the data collected within the larger mDAS study as part of the analyses in this sub-study. Patients are allowed to decline and still participate in this portion of the research.**

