## 12.1 Additional Statistical Considerations for mDAS Sub-study

[name] will receive statistical/analytic support from the Methodology Research Core at the Institute for Health Research and Policy (IHRP) and statistician [name]. Descriptive statistics will be summarized as mean (standard deviation) or median (range) for continuous variables, and as frequencies (proportions) for categorical variables. We will address the three specific aims as follows:

**Aim 1:** Descriptive statistics will be calculated for the PROMIS as well as sleep duration based on text-message responses. Response rates will be quantified per individual and overall in aggregate. Interviews will provide an inventory of potential barriers to sleep in the home (e.g., presence of television in bedroom). These will be categorized and quantified. Differences in race/ethnicity within the descriptive data will also be compared.

**Aim 2:** Feasibility and acceptability of using the Actiwatch to collect objective sleep data will be based on the average number of days and amount of time per day the Actiwatch was worn. In addition, research personnel will obtain qualitative information regarding barriers to wearing the device in the semi-structured phone interview. Drs. [name], [name], and [name] will collaboratively determine a coding scheme to describe issues discovered.

**Aim 3:** Independent and dependent variables will be explored via histograms to identify extreme values and assess normalcy (some Actiwatch data may yield spurious values). We will determine correlations between subjective text-message sleep diary and objective Actiwatch data (e.g., total sleep time and bouts of waking after sleep onset). In addition, we will examine correlations between sleep parameters (e.g., total sleep time) and hemoglobin A1c, depression, quality of life, and sedentary behavior. For continuous variables, Pearson correlations will be calculated (and Spearman rank for non-parametric variables). Partial correlation models will include covariates such as patient age, gender, race/ethnicity, income, and education level. We will explore additional models that include the number of days the Actiwatch device was worn. All hypothesis tests will be 2-sided with a significance level of 0.05.

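### The Actiwatch wear summaries in Section 12.1 do not show whether the watch was worn at night, so they do not answer the sleep half of sub-study Aim 2

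*Protocol*

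**What the plan says.** Section 3.1 gives the second sub-study aim as "To evaluate the feasibility and acceptability of objectively measuring sleep quality, duration, and patterns and sedentary behaviors via mHealth". It names two targets: sleep, which is recorded in bed, and sedentary behaviour, which is recorded while awake.

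Section 12.1 (Aim 2) takes up the sleep target. Its subject is "Feasibility and acceptability of using the Actiwatch to collect objective sleep data", and it says that these "will be based on the average number of days and amount of time per day the Actiwatch was worn". The only other source it names is an interview: "research personnel will obtain qualitative information regarding barriers to wearing the device in the semi-structured phone interview". It gives no count of nights and no cut-off.

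Under Aim 3, Section 12.1 plans to explore "additional models that include the number of days the Actiwatch device was worn".

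On the wear period, the data collection steps for the sub-study say "Study participants will wear a wrist actigraphy for 7 days and 7 nights". Sections 3.1, 5.1 and 7.0 also give seven days. In the sub-study part of Section 6.1, item 5 asks participants "to evaluate his or her sleep for 9 days", while item 6 of the same list gives seven days of wear, day and night.

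**The concern.** Whether a wrist device can record sleep at home depends on whether it is on the wrist in bed and gives a record that can be scored. Days worn and hours worn per day are general measures of compliance. A day counts as worn whether the watch was on at noon or at midnight, and an hour awake counts the same as an hour asleep.

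Section 2.1 makes the feasibility and acceptability of mobile sleep assessment the supplement's overall objective and describes the findings as preliminary data for later sleep research. A high wear figure could be carried into that work as evidence that sleep can be measured this way, although the figure leaves open how many nights were captured.

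**Working it through.** **Inputs.** Wear period: 7 days and 7 nights (Sections 3.1, 5.1 and 6.1). Sub-study size: 40 (Section 5.1). Time in bed: the protocol gives no planning value, so I assume 8 hours, with a range of 6 to 9. The protocol states no feasibility figure or threshold, so there is nothing to reproduce.

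**One participant.** Let *s* be hours in bed.

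- Watch removed at every bedtime: days worn = 7, hours per day = 24 − *s*, nights recorded = 0.
- Watch kept on in bed and removed for *s* waking hours: days worn = 7, hours per day = *s* + (24 − 2*s*) = 24 − *s*, nights recorded = 7.

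| Hours in bed (assumed) | Days worn, both | Hours per day, both | Share of 24 h | Nights: removed at bedtime | Nights: kept on in bed |
|---|---|---|---|---|---|
| 6 | 7 | 18 | 75% | 0 | 7 |
| 7 | 7 | 17 | 71% | 0 | 7 |
| 8 | 7 | 16 | 67% | 0 | 7 |
| 9 | 7 | 15 | 62.5% | 0 | 7 |

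At 8 hours in bed, mixing the two patterns across the week keeps the average at 16 hours a day and gives any number of nights from 0 to 7.

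**The group.** Suppose a fraction *f* of wearers remove the watch at bedtime (8 hours) and the rest wear it for all 24. Mean days = 7, mean hours = 24 − 8*f*, mean nights = 7(1 − *f*).

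| *f* (assumed) | Mean days | Mean hours per day | Mean nights of 7 |
|---|---|---|---|
| 0 | 7 | 24 | 7 |
| 25% | 7 | 22 | 5.25 |
| 50% | 7 | 20 | 3.5 |
| 75% | 7 | 18 | 1.75 |
| 100% | 7 | 16 | 0 |

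Days worn does not respond at all. Hours per day falls by one third at most (24 to 16) while the sleep record falls to nothing.

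**A second illustration.** Take 23 hours a day for those who keep the watch on at night and 15 for those who do not (both assumed). With a share *q* removing it, mean hours = 23(1 − *q*) + 15*q*, and participants with any sleep record = 40(1 − *q*):

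- *q* = 10%: 22.2 hours, 36 participants
- *q* = 25%: 21.0 hours, 30 participants
- *q* = 40%: 19.8 hours, 24 participants

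**The case against.** **Night wear is already required.** Participants are told to wear the watch day and night, and Section 5.1 allows removal only for submersion in water. Removal at every bedtime by everyone would be a wholesale breach, and the shares used above are assumptions, not figures from the protocol. This is fair as to how likely the extreme case is. It does not rescue the measure: the instruction says what participants are asked to do, and a feasibility assessment has to show what they did.

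**The gap would surface elsewhere.** The phone interview may reveal bedtime removal. A participant without night records would have no actigraphic sleep values to pair with the diary in Aim 3. Hours per day is not wholly blind either: in the illustration it drops from 23 to 15 for a bedtime remover. All this is true, but none of it puts a count of nights into the stated feasibility measure.

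**This is analysis-plan detail.** Scoring rules for a valid night can reasonably be left to an analysis plan. Here, however, the protocol names its measure, and the named measure does not match the sleep target of the aim.

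**Stronger readings that the protocol does not support.**

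- A reader might infer that the watch could be declared feasible wrongly. Section 12.1 sets no pass mark, so there is no threshold to pass.
- A reader might infer from item 5 of the sub-study list in Section 6.1 that the length of wear is unsettled between 7 and 9 days. Every statement about wear gives seven days, and elsewhere the ninth day marks the closing phone call. Item 5 is loose wording, and the denominator stays at 7.
- A reader might infer that the Aim 3 results are compromised. The models with days worn are an exploratory addition to the main correlations.
- A reader might infer that people who wear the watch only in bed are scored unfairly. Aim 2 also covers sedentary behaviour, for which bed-only wear does fall short.

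**Conclusion.** The point holds as a mismatch between aim and measure. The two stated summaries cannot tell a week with no nights recorded from a week with all seven: at 8 hours in bed, 7 days and 16 hours a day fits anything from 0 to 7 nights. The size depends on the assumed time in bed (6 to 9 hours gives 18 to 15 hours of wear with no nights) and on how many participants remove the watch at bedtime, which the protocol does not let us estimate. That the summaries do not identify nights depends on neither assumption.

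The point is minor. It concerns an exploratory, 40-person sub-study and leaves the parent trial's outcomes untouched.

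**What to change.** In Section 12.1, Aim 2:

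- Report for each participant how many of the 7 nights have a scorable Actiwatch sleep interval, using the bed and rise times from the sleep diary to locate the night, and give the distribution across participants.
- Report waking hours of wear per day separately, for sedentary behaviour.
- Keep the present wear summaries as descriptive figures.

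In the exploratory Aim 3 models that involve sleep parameters, use the number of scorable nights in place of, or alongside, the number of days worn.

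Reconcile the nine-day wording in item 5 of the sub-study list in Section 6.1 with the seven-day wear period.

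The cost is a change of wording and slightly more analysis. No new data are needed: Aim 3 already calls for sleep values from the Actiwatch, and the diary already asks for bed and rise times. The downside is that the reported feasibility figure may be less favourable.

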## **4.0 Eligibility**

### **4.1 Inclusion Criteria**

- Self-identified as Latino/Hispanic or African-American
- Verbal fluency in English or Spanish
- Latest A1c  $\geq$  8.0% (within 3 mo)
- History of Type 2 Diabetes (> 1 year)
- Between the ages of 21 and 75 years
- Unlimited mobile phone/text messaging plan with ability to reply to text messages
- Home environment capable of video conferencing with wireless signal per patient's report of cell phone reception in the home
- Receives primary care at clinical site for at least one year, with one visit during past year
- Able and willing to provide informed consent (agree to data collection requirements, accept randomization, agree to home visitation with HC and pharmacist involvement, and participate for two years)

## 4.2 Exclusion Criteria

- Unable to verbalize comprehension of study or impaired decision making
- Lives outside Chicago (3+ months/year)
- Family/household member already participating in same study
- Plans to move from the Chicago area within the next two years
- Pregnant or trying to get pregnant
- Currently receiving regular pharmacist support through Medication Therapy Management or equivalent
- Unable to send/read text messages on mobile phone
- History of, or planned, gastric bypass or transplant surgery
- History of bipolar or psychotic disorder
- Other severe comorbidities that require complex, aggressive, or palliative treatment, e.g., stage 4 or greater renal disease, liver failure, cancer (other than nonmelanoma skin cancer), terminal illness
- Investigator discretion for safety concerns

Supplement Sleep sub-study is offered only to English-speaking participants but no additional inclusion/exclusion apply.

## 5.0 Subject Enrollment

University of Illinois Hospital and Health Sciences System (UI Health) includes both inpatient and outpatient facilities serving a diverse population in Chicago. UI Health has 19 ambulatory centers staffed by Family Medicine and Internal Medicine PCPs and includes Mile Square FQHCs where care is provided independent of ability to pay. Four to six clinical sites will participate. All sites share access to the EMR, Cerner Powerchart, and employ clinical pharmacists through the UIC College of Pharmacy Practice.

We will employ the following recruitment/enrollment methods:

1. **Passive Advertising:** We will distribute study advertisement materials throughout UI Health, including clinical environments. Individuals will call research assistants (RAs) for eligibility assessment by phone.
2. **Active Recruitment from Registries:** The research assistants will work from a physician-approved list of patients with diabetes and A1c  $\geq 8$  identified from the electronic medical record. We will send letters informing patients that they may be eligible for the study and may opt-out of further contact. After one month, those who do not opt out will be contacted by the RAs to assess interest and eligibility.
3. **Active Recruitment in Clinical Sites:** On-site RAs will receive additional referrals directly from staff or patients interested in the study. In these situations, RAs will discuss the

study and assess eligibility in a private exam room within the clinic before or after a clinical encounter.

4. Diabetes Health Registry: RAs will call by phone individuals completing the Diabetes Health study (IRB 2011-0099) who indicated willingness to be contacted regarding future studies.

Chart review will be performed to establish eligibility (type 2 diabetes and A1c 8% or higher in past three months). An RA will complete an initial screening interview with the potential patient, either over the phone or in person in the participating clinics. RAs will ask screening questions (see Eligibility Screening attachment) and document the screening and eligibility (see Screening and Contact Information Sheet attachment). If the patient is eligible and interested, the RA will review the study in detail, using an IRB approved consent form as guidance. The RA will inform patients that the research is being conducted to improve medication management in diabetes care and to find out if pharmacists and health coaches help people reach goals of therapy. The RA will discuss the study protocol in detail as part of consent procedures and use the “teach back” method to ensure participant comprehension. The RA will clarify that the research procedures are separate from routine clinical care and participation is completely voluntary. All subjects must have a mobile phone with text messaging plan. Any individuals without an unlimited plan will not be reimbursed for text charges. The RA will confirm the patient’s eligibility and willingness to meet with a health coach in their home. They will then obtain informed consent and HIPAA authorization. The patient will be offered a copy of the consent form for their own convenience.

Participants will then complete baseline data collection at the UIC Clinical Interface Core. All screening and study data will be recorded in REDCap. Screening reports will provide investigators with information regarding recruitment progress and reasons for ineligibility.

## **5.1 Additional Subject Enrollment and Methods for mDAS Sub-study Sleep Supplement**

At the end of a regularly scheduled data collection point for the larger R01 study, English-speaking participants will be asked if they are interested in hearing the details of a sleep study (mHealth Supplement). Interested participants will be given a brief overview of the study and if they remain interested, at that time they will be fully consented for participation. If they are interested but unable to stay for the consenting process and/or additional data collection, another visit will be set up. Otherwise, after providing written informed consent, participants will complete a series of sleep related questionnaires that will be entered directly into REDCap. After completing the questionnaires, participants will be given a Philips Actiwatch with instructions for use. They will be asked to wear the watch for 7 consecutive days taking it off only if they are going to submerge it in water. They will also be reimbursed \$10 for their additional time. Each day during the 7 day sleep period, they will answer daily questions through a survey about the previous night’s sleep quality and process. The participants will have the option of a) completing the consensus sleep diary survey questions via text using the myTapp messaging system, or b) completing a web-based online sleep diary survey using a

secure application such as REDCap or Qualtrics. If the participants do not respond to the text message link, then research personnel will attempt to call the participant once to complete the day's sleep diary. At the end of the 9 days, participants will be contacted by telephone to complete a brief post-study assessment (see measures) and to schedule a day/time to return the actiwatch. Participants will be given the option of coming into the CRC to drop off the Actiwatch or they can have an RA come to their house to pick up the device. They will receive an additional \$30 when the Actiwatch is returned. Recruitment goal is 40 individuals; although we expect to have to approach at least 60 in order to get 40 who will complete the study.

## **6.0 Study Design and Procedures**

A randomized, controlled trial will evaluate the effectiveness of *mDAS* delivered by a clinical pharmacist and HC versus a usual care group. We will recruit 220 patients from UI Health. We recognize that all participants will have uncontrolled diabetes and require additional support from their healthcare team. Consequently, our usual care group will receive additional resources to meet basic standards of diabetes care and establish clinical equipoise between the two study groups. The usual care group will receive a referral to a diabetes educator and clinical pharmacist for medication reconciliation. These individuals are on staff and available to any patient, yet under-utilized. This group will receive a one-page contact sheet with the names and phone numbers of their local healthcare team as well as paper-based, low-literacy diabetes educational information. After one year, patients who have completed *mDAS* will be monitored for an additional year with usual care to evaluate maintenance, while the usual care patients receive *mDAS*. After recruitment, subjects will be randomized to receive either: (1) *mDAS* delivered by a clinical pharmacist and HC via home visits, videoconferencing, and text messaging; or (2) usual care. Study condition allocation will be completed after consent and baseline data collection. Using the REDCap Randomization Module, a random sequence of 220 subject assignments will be used. Blocked randomization (with varying block sizes) by clinical site, ethnic group (African-American and Latino), and gender will balance the proportion of participants.

